### 5.2. Interim Analysis

### 5.2.1 Interim Analysis, Data Monitoring and Stopping Rules

During the period of recruitment into the study, interim analyses of the baseline and follow up data will be supplied, in strict confidence, to the chairman of the data monitoring committee, along with any other analyses that the committee may request. In the light of these analyses, the data monitoring committee will advise the chairman of the steering committee if, in their view, the randomised comparisons have provided both (i) 'proof beyond reasonable doubt' that for all, or some, the treatment is clearly indicated or clearly contra-indicated and (ii) evidence that might reasonably be expected to materially influence future patient management.

Appropriate criteria of proof beyond reasonable doubt cannot be specified precisely, but the DMC will work on the principle that a difference of at least 3 standard errors in an interim analysis of a major outcome event (e.g. death from all causes or independent survival at six months) may be needed to justify halting, or modifying, a study before the planned completed recruitment. This criterion has the practical advantage that the exact number of interim analyses would be of little importance, and so no fixed schedule is proposed. Following a report from the DMC, the steering committee will decide whether to modify entry to the study (or seek extra data). Unless this happens however, the steering committee, the collaborators and central administrative staff will remain ignorant of the interim results.

The Chairs of the DMCs of FOCUS, AFFINTY and EFFECTS will communicate regularly to share any concerns about the accruing data and will share data if indicated. Therefore the DMC will potentially have access to all available information when making its recommendations. This aims to maximise patient safety.

### 5.2.2 Interim Analysis and Sample Size Adjustment

The trial steering committee (TSC) will review the target sample size and adjust this based on:

- Advice from the DMC
- Accruing data on
  - the enrolment into specific pre-specified subgroups
  - completeness of follow up
  - distribution of mRS categories in the population of enrolled subjects (i.e. both treatment groups combined), overall and in specific patient categories (e.g. those with motor deficits, aphasia, etc)

For example, if the distribution of mRS is different to that anticipated, then the sample size might need to be increased. This approach has the advantage that such sample size adjustments can be made without reference to the accumulating unblinded data, and avoids the need for conditional power calculations which can be unreliable.

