## 2. Introduction

Fluoxetine Or Control Under Supervision (FOCUS) is a parallel-group multicentre randomised trial to establish the effect(s) of routine administration of Fluoxetine in patients with a recent stroke. The trial aims to recruit at least 3000 patients. Patients are randomised via a web based randomisation system utilising a minimisation algorithm with a random component to receive Fluoxetine 20mg once daily or matching placebo capsules for 6 months and follow up at 6 and 12 months.

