## 6. Summary of DMC Report Data

All categorical data [including binary data] will be presented as numbers and percentages broken down by randomised treatment. Where data are continuous descriptive statistics will be presented [N, mean, sd, min, max, median, Q1, Q3] broken down by randomised treatment.

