### 6.6. Outcomes

**Primary outcome:** Number and percent of patients in each treatment group will be presented by ordinal mRS. Odds ratio, 95% CI for odds ratio will be presented for both adjusted and unadjusted analysis, as described for the final analysis. Adjustment will only be performed if sufficient data have accrued.

**Secondary outcomes:** For binary outcomes odds ratio, 95% CI for odds ratio will be presented for both adjusted and unadjusted analysis, as described for the final analysis. Adjustment will only be performed if sufficient data have accrued.. For continuous outcomes descriptive statistics will be presented [N, mean, sd, min, max, median, Q1, Q3] broken down by randomised treatment.

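### SAP 5.2.2 lets unrestricted advice from a DMC that sees results by arm change the sample size, yet describes the approach as needing no unblinded data; that is true only of the pooled inputs

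*SAP*

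**What the plan says.** Section 5.2.2 gives the decision to the steering committee: "The trial steering committee (TSC) will review the target sample size and adjust this based on" a list of inputs. The first is "Advice from the DMC", with no qualification. The rest are accruing data on subgroup enrolment, completeness of follow-up, and the "distribution of mRS categories in the population of enrolled subjects (i.e. both treatment groups combined"). After an example in which an unexpected mRS distribution leads to a larger trial, the section says that the approach has the advantage that "such sample size adjustments can be made without reference to the accumulating unblinded data", and that it avoids conditional power calculations.

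Other sections show what the DMC knows. Under section 6, categorical data in its report are "presented as numbers and percentages broken down by randomised treatment". Section 6.6 adds for the primary outcome: "Number and percent of patients in each treatment group will be presented by ordinal mRS", with odds ratios and 95% confidence intervals. Section 5.2.3 says that the statistician who prepares the report is unblinded. Section 5.2.1 lets the DMC request further analyses and share data with the DMCs of two parallel trials.

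Section 5.2.1 also sets a firewall. Unless a DMC report leads the TSC to modify entry or seek extra data, "the steering committee, the collaborators and central administrative staff will remain ignorant of the interim results". The only size stated is in section 2: "The trial aims to recruit at least 3000 patients".

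**The concern.** The list of inputs and the claimed advantage do not fit together. A committee that has seen the odds ratio by arm cannot be assumed to give advice on size that is independent of it. If the advice depends on the interim effect, the final sample size depends on the data being tested, and the usual test at 1.96 no longer has a guaranteed 5% level.

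There are two further consequences. A change of target made on DMC advice may tell the TSC something about the interim trend, by a route that has neither the proof criteria nor the 3-standard-error guide of section 5.2.1. And if the target were changed on DMC advice, the trial could not show from its own plan that the change was made blind.

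**Working it through.** **1. The inputs compared with the claim**

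| Input in 5.2.2 | Limited to pooled or blinded data? | Claim holds? |
|---|---|---|
| Advice from the DMC | No limit stated; the DMC sees mRS and odds ratios by arm (6, 6.6) | Not assured |
| Subgroup enrolment | Baseline counts; no outcome by arm needed | Yes |
| Completeness of follow-up | No outcome by arm needed | Yes |
| mRS distribution | Expressly both groups combined | Yes |

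The claim fails for one input of four.

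**2. What could follow for type I error**

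The SAP gives no figure here to reproduce. It states no alpha, look schedule or resizing rule, and the protocol, which may hold these, is not at hand. The following are assumptions: a two-sided 5% level, one look at fraction t = 0.5 of the planned information, and an unadjusted final test at c = 1.96.

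Let z be the interim statistic and T the final information as a multiple of that planned. Under no treatment effect, the chance of rejecting at the end given z is

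R(z, T) = 1 − Φ[(c√T − z√t)/√(T − t)] + Φ[(−c√T − z√t)/√(T − t)].

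The type I error of a rule T(z) is the integral of φ(z)·R(z, T(z)) over z.

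*Checks.* T = 1 always gives 0.0500. T = 2 chosen independently of z, as a pooled-data decision is modelled, also gives 0.0500. So the plan's description is sound for the pooled inputs.

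*Doubling whenever |z| < 1.* Take z = 0. With T = 1, R = 2 × [1 − Φ(1.96/√0.5)] = 2 × [1 − Φ(2.772)] = 0.0056. With T = 2, R = 2 × [1 − Φ(1.96√2/√1.5)] = 2 × [1 − Φ(2.263)] = 0.0236. Integrated over |z| < 1, the contribution rises from 0.0095 to 0.0209. The region |z| ≥ 1 is unchanged at 0.0405. The total is 0.0209 + 0.0405 = 0.0614, that is 0.061 (0.06135 before rounding). A 1.5-fold increase instead gives 0.057.

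*Conditional-power rules.* Conditional power under the current trend is CP = 1 − Φ[(c − |z|√t − (|z|/√t)(1 − t))/√(1 − t)]. Doubling when CP lies in the stated window gives:

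| CP window | Type I error |
|---|---|
| 0.1 to 0.5 | 0.052 |
| 0.1 to 0.8 | 0.049 |
| 0.3 to 0.8 | 0.047 |
| 0.5 to 0.8 | 0.047 |

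A simulation of the 0.1 to 0.5 window (4 million trials) also gave 0.052.

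*Worst case.* Choosing at each z the T that maximises R gives an upper bound:

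| Permitted final size (multiple of plan) | Upper bound |
|---|---|
| 1 to 1.5 | 0.058 |
| 1 to 2 | 0.062 |
| 0.75 to 1.5 | 0.066 |
| 0.55 to 2 | 0.084 |

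The last two rows require that the size may be reduced.

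**The case against.** The strongest reply is that the sentence is being read too broadly. It directly follows the mRS example, whose input is pooled, and it says that adjustments can be made without unblinded data, not that every adjustment will be. For the pooled inputs it is correct. This narrows the point but does not remove it: the advantage is claimed for the approach as a whole, and that approach lists DMC advice without limit.

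A reader might infer that the plan fails to keep a promised type I error. The documents do not support that. Section 5.2.2 gives no type I error guarantee for resizing, describes no effect-driven rule and sets conditional power aside. DMC advice might rest on pooled data or on the systematic reviews sent to it under 5.2.4. Nor does knowledge of the interim effect always inflate the error: three of the four conditional-power rules above fall below 0.05. The rule of doubling when |z| < 1 enlarges only trials with little signal (CP at most 0.22) and lies close to the worst case for a doubling cap, so it is not typical.

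A reader might also quote the figures of 0.066 and 0.084. These need a reduction in size, whereas the only example in 5.2.2 is an increase and section 2 words 3000 as a minimum. The word adjust does not exclude a reduction, but nothing in the SAP points to one.

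Finally, a reader might infer that the firewall is missing. It is not. Section 5.2.1 keeps interim results from the TSC, and 5.2.3 has a blinded statistician consider statistical issues during the trial. Advice to enlarge would not reveal which arm is ahead. What stands is that such advice might hint at a trend.

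**Conclusion.** Section 5.2.2 is internally inconsistent: its no-unblinded-data property holds for the pooled inputs and is not assured for DMC advice. On that one route type I error is not guaranteed if the advice reflects the interim effect and the final test is unadjusted. Under the assumptions above, with the size at most doubled, the error runs from about 0.047 to 0.052 under conditional-power rules, and no increase-only rule takes it above 0.062. Larger values need a cut in size. Both inflation and a signal to the TSC are possibilities that the wording leaves open; neither is shown to occur. The possible error is modest, but so is the cost of closing the gap, and the change is worth making.

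**What to change.** In section 5.2.2:

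- Limit DMC advice on sample size to pooled information (both arms combined) or external information, such as the reviews in 5.2.4. Removing DMC advice altogether would go further than needed, because these are legitimate inputs.
- State that the DMC's stopping and safety role under 5.2.1 is unchanged.
- State that any size change informed by results by arm will be declared as unblinded and analysed with a method that controls type I error. One example is a combination test, √w·Z₁ + √(1 − w)·Z₂, where Z₁ and Z₂ come from patients before and after the change and the weight w is fixed in advance.

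With the first change in place, the sentence on unblinded data becomes true as written. The cost is SAP wording only. The small downside is that the DMC can no longer informally steer sample size from the interim effect.

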### 5.2.3. Practical Measures to Minimise Bias

In producing the DMC report the trial statistician will be unblinded to treatment allocation although the primary outcomes will be verified by a second statistician who will be aware of which group participants are in but not what treatment each group received. In addition to that [name] will be involved as a blinded statistician and any statistical issues that require to be addressed through the course of this trial will be considered by her in a blinded manner.

### 5.2.4. Other evidence

Any relevant updated systematic reviews will be circulated to the DMC, and the results will be added into a systematic review at the end of the trial. There is one relevant Cochrane review: Mead GE, Hankey GJ, Kutlubaev MA, Lee R, Bailey M, Hackett ML. Selective serotonin reuptake inhibitors (SSRIs) for stroke. Cochrane Database of Systematic Reviews 2011, Issue 11. Art. No.: CD009286. DOI: 10.1002/14651858.CD009286

## 6. Summary of DMC Report Data

All categorical data [including binary data] will be presented as numbers and percentages broken down by randomised treatment. Where data are continuous descriptive statistics will be presented [N, mean, sd, min, max, median, Q1, Q3] broken down by randomised treatment.

### 6.1. Recruitment

Standard accrual plot, and plot of number of patients recruited each quarter. Table showing number of centres recruiting patients.

### 6.2. Trial randomisation flow chart

For each form, % received, % not received + reasons why forms missing.

### 6.3. Success of minimisation, and baseline data

**Minimisation**: Check minimisation is successfully balancing on minimisation factors.

**Other baseline data [collected on randomisation form]:** Check treatment balanced by sex, ethnicity, whether patient is an inpatient, depression, diabetes, previous CHD, previous ischaemic stroke/TIA, previous intracranial bleeding, history of GI bleeding, hyponatraemia, bone fractures, current mood [both yes, 1 yes, none yes], recent intracerebral bleeding, type of stroke/OCSP classification and total NIHSS.

**Other data collected post treatment [collected on discharge form]:** Check the following are equally balanced by treatment group: final diagnosis of randomising event, post randomisation non-trial medication, discharge destination and in-hospital compliance variables for inpatients [received any trial medication, taking till death/discharge, reasons for not taken till death or discharge and doses missed].

### 6.4. Protocol violations, compliance and blinding

**Inclusion/Exclusion violations:** quantify the number and % of participants randomised >15 days after stroke onset, diagnosis of subarachnoid haemorrhage

**Compliance**: Each participant will be issued with 6 months supply of trial medication, at 6 months they will be asked if they have taken all capsules, asked on average how often they took capsules and asked the reasons for stopping as well as date of stoppage.

Our main measure of compliance will be the patient reported completion of medication. However at the end of each participants involvement any unused medication will be returned and counted. A check on the patient reported compliance will be determined based on the number of pills not returned and the duration each participant has spent in the trial.

**Blinding:** quantify the number of patients who required unbinding of study medication during the trial by treatment arm and where available present the reasons for unblinding.

### 6.5. Adverse events

Adverse events will be analysed by treatment as received, not by treatment as allocated. Any adverse event occurring during initial in-patient stay should be recorded on the discharge form: further stroke, acute coronary event, upper GI bleed, fall with injury, new fractures, definite epileptic seizure, symptomatic hypoglycaemia, hyperglycaemia, hyponatraemia, new depression [diagnosis/treatment], new antidepressants given, suicide/self harm.

Post discharge the same list of events will be captured as part of the patient update. Any serious adverse events will be captured and information presented by treatment received.

In hospital and post discharge AEs will be quantified and presented as number and % of patients broken down by treatment received.

### 6.6. Outcomes

**Primary outcome:** Number and percent of patients in each treatment group will be presented by ordinal mRS. Odds ratio, 95% CI for odds ratio will be presented for both adjusted and unadjusted analysis, as described for the final analysis. Adjustment will only be performed if sufficient data have accrued.

**Secondary outcomes:** For binary outcomes odds ratio, 95% CI for odds ratio will be presented for both adjusted and unadjusted analysis, as described for the final analysis. Adjustment will only be performed if sufficient data have accrued.. For continuous outcomes descriptive statistics will be presented [N, mean, sd, min, max, median, Q1, Q3] broken down by randomised treatment.

## 7. Final analysis

### 7.1. Primary outcome

Comparison of Modified Rankin score [mRS] at six-months post randomisation by treatment group where mRS treated in its full ordinal format [scores of 0,1,2,3,4,5,6]. This will be examined using an ordinal logistic regression and will be performed in both an unadjusted manner and also adjusted for factors in the baseline minimisation (as recommended by the Draft CPMP guidelines, December 2001). We will present common odds ratios using the proportional odds method and for the unadjusted analysis we will also present the individual dichotomies.

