## 3. Statistical methods from protocol

Our primary analyses will retain patients in their original assigned treatment groups.

Our primary analysis will compare the mRS at the six month follow up using an ordinal analysis adjusted for any baseline imbalance in those factors included in our minimisation algorithm.

We will compare the mRS at the twelve month follow up to establish if any benefits observed at 6 months are maintained.

Secondary analyses will compare the two treatment groups with respect to the following outcomes at 6 and 12 months.

- Survival (Logistic regression)
- EQ5D-5L (HRQOL) to generate utilities
- SIS (for each of 9 domains on which the patient scored 0-100)
- MHI 5 (mood)
- Fatigue (Vitality subscale of SF36)
- New diagnosis of depression requiring treatment with antidepressants
- Adverse events
- Adherence to trial medication

Longer term survival will be analysed with Cox proportional hazards model

We will also perform analyses of potential mediating factors e.g. the role of depression. We will seek to answer the question whether any benefits are mediated by improvement in mood (based on MHI 5 and also whether any apparent loss of benefits in mRS or SIS between 6 months to 12 months is because of a deterioration in mood.

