## 4. Study Methods

### 4.1. Randomisation and blinding

Having obtained consent, the randomising person collects the baseline data necessary to complete a randomisation form and enters the patient’s baseline data into our computerized central randomisation service by means of a secure 24/7 Web interface or a telephone call to the trial office during office hours. After the computer program has checked these baseline data for completeness and consistency it allocates that patient a unique study identification number and a treatment pack number which corresponds to either Fluoxetine or Placebo. The system applies a minimisation program to achieve balance for four factors:

- Delay since stroke onset [2 – 8 days v 9 – 15 days]
- Predicted outcome at 6 months based on Counsell 2002 [predicted probability of being alive & independent at 6 months of 0 – 0.15 v 0.16 – 1]
- Presence of a motor deficit [yes v no – where deficit is NIHSS5 (right or left) >0, NIHSS6 (right or left)>0 or NIHSS7 >0]
- Presence of aphasia [NIHSS question 9: 0 v 1 – 3 ]

The minimisation algorithm randomly allocates the first patient to a treatment, but allocates each subsequent patient to the treatment that leads to the least difference between the treatment groups with respect to the prognostic factors (Altman 2005). To ensure that we retain a random element to treatment allocation, patients will be allocated to the group which minimizes differences between groups with a probability of 0.8. The system contains a list of treatment codes for each centre and which match the stocks held at that centre. At the end of the session each patient is allocated a treatment code which corresponds to either an active (f.luoxetine 20mg once daily) or placebo treatment pack which contains six months supply of capsules held at that centre. The randomisation system will take account of the drug stocks held locally to firstly ensure the allocated treatment is available and second to minimise wastage.

The patient, their families, the healthcare team including the pharmacist and anyone involved in outpatient assessments will be blinded to the treatment allocation.

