### 4.3.6. Six Simple variable (SSV) model

Based on the work ‘C.Counsell, M.Dennis, M.McDowall,C.Warlow. Validation of New Prognostic Models Predicting Outcome After Acute and Subacute Stroke : Development and Validation of New Prognostic Models. *Stroke* 2002, 33:1041-1047’ we can calculate the probability of being alive and independent at 6-months using the following model:

[figure not shown]

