### 7.2. Secondary outcomes - binary

Where the outcome of interest is binary, comparison by treatment group will be examined using a binary logistic regression and will be adjusted for factors used in the minimisation algorithm, unadjusted odds ratios will also be presented. In addition the results will be presented as relative risks with 95% CI, calculated from the odds ratio [using methods described by Deeks JJ, Higgins JPT, Altman DG (editors). Chapter 9: Analysing data and undertaking meta-analyses. In: Higgins JPT, Green S (editors). Cochrane Handbook for Systematic Reviews of Interventions. Version 5.0.1 [updated September 2008]. The Cochrane Collaboration, 2008. Available from [www.cochrane-handbook.org](http://www.cochrane-handbook.org/).] and absolute risk differences with 95% CI.

1. Modified Rankin score at six-months [mRS 0-2 v mRS 3-6].
2. Death from any cause by six-months.
3. Death from any cause by twelve-months.
4. New diagnosis of depression since randomisation by six-months.
5. New diagnosis of depression since randomisation by twelve-months.

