### 7.6. Pre-specified sub group analysis

Comparison of mRS at 6-months based on Ordinal analysis will be split by the following sub-groups: age [<70, ≥70], baseline probability of being alive and independent at 6-months [<0.15, 0.16-1 based on Carls model], type of stroke [ischaemic, haemorrhagic], patient able to provide own consent [yes, no] adjusting for baseline motor impairment [yes/no], baseline aphasia [yes/no] and baseline depression [yes/no].

Motor impairment: In patients with motor impairment resulting from the initial stroke [where motor impairment is defined as above] is there a difference in the motor function at 6 months [as measured by SIS, question 12, 17, 18 on follow up)]. Is this maintained at 12 months? Linear regression analysis will be performed on the baseline to 6-month change and separately for the 6-month to 12-month change both unadjusted and also adjusted for factors in the minimisation.*.*

Communication impairment: In patients with communication impairment resulting for the initial stroke [where communication impairment is defined as above on NIHSS] is there a difference in the communication function at 6 months [as measured by SIS, question 15]. Is this maintained at 12 months? This analysis will be performed unadjusted and also adjusted for factors in the minimisation.

Linear regression analysis will be performed on the baseline to 6-month change and separately for the 6-month to 12-month change both unadjusted and also adjusted for factors in the minimisation.

Mood: Is there a relationship between outcome [as defined by mRS at 6-months] and mood [measured using MHI5] and is this relationship affected by Fluoxetine?

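### Adjustment for predicted outcome uses only a two-level split, and the mRS subgroup models in 7.6 leave it out: a valid plan that gives up power

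*SAP*

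**What the plan says.** Section 3, carrying text from the protocol, plans the primary comparison "using an ordinal analysis adjusted for any baseline imbalance in those factors included in our minimisation algorithm". Section 7.1 turns this into a proportional-odds model, unadjusted and "also adjusted for factors in the baseline minimisation". Sections 7.2 (binary), 7.3 (twelve-month mRS), 7.4 (continuous) and 7.5 (Cox) use the same factors.

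Section 4.1 lists the four factors: delay, predicted outcome, motor deficit and aphasia. Predicted outcome appears there as "predicted probability of being alive & independent at 6 months of 0 – 0.15 v 0.16 – 1". Section 4.3.6 describes the six simple variable (SSV) model behind it: "we can calculate the probability of being alive and independent at 6-months using the following model". Section 4.1 also says that the study number and treatment pack are given only "After the computer program has checked these baseline data for completeness and consistency".

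Section 7.6 compares six-month mRS within four subgroupings, "adjusting for baseline motor impairment [yes/no], baseline aphasia [yes/no] and baseline depression [yes/no]". One of the four is the predicted-outcome split itself. The SIS analyses for motor and communication impairment, in the same section, are run unadjusted and also adjusted for the minimisation factors.

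**The concern.** With one cut near 0.15, a patient predicted 0.17 and one predicted 0.95 enter the model as the same kind of patient. If the prediction works at all, most of its information on mRS lies within the upper category and is not used. In a proportional-odds model, leaving out prognostic information pulls the treatment odds ratio towards 1 and lowers power, even with perfect balance between the arms.

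The mRS subgroup models go further. Apart from the subgrouping that uses the split, they contain no predicted outcome. They also have no delay term, and they add depression, which is not a minimisation factor. Odds ratios are non-collapsible, so a subgroup odds ratio from this set and the overall adjusted odds ratio can differ with no heterogeneity of effect. At stake are power in the main comparison and in already weaker subgroup comparisons, and a clean reading of the subgroup results beside the overall one.

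**Working it through.** **Is the continuous value available?** Allocation uses the two-level category, the category comes from the SSV probability, and allocation follows a completeness check. So the probability can be calculated for everyone randomised, and using it loses no patients.

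**What form will the model use?** Section 7.1 refers to the minimisation factors, section 4.1 defines this one as two levels, and no section mentions a continuous term. Two levels is the natural reading.

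**How much is lost?** The SAP gives N (at least 3000, section 2) but no effect size, power, mRS distribution or predictor strength, so it offers no figure to reproduce. I simulated proportional-odds data with 1,500 patients per arm and 200 data sets per scenario.

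Assumptions, none of them from the SAP:
- common odds ratio 1.2 (log odds ratio 0.182), two-sided 5% test
- cumulative proportions for mRS 0 to 5 of 8, 20, 35, 60, 80 and 90%
- normal logit of the predicted probability, with mean and SD (−1, 1.5), (−0.5, 1.8) or (−1.7, 1.5), which puts 31, 25 or 49% of patients at or below 0.15
- slope of mRS on that logit 0.5, 0.8 or 1.0
- motor deficit and aphasia mildly correlated with the prediction, with effects 0.3 and 0.2 on the logit scale
- delay and depression left out

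Formulas: power = Φ(mean z − 1.96); effective sample size relative to continuous adjustment = (z of the model / z of the continuous model)².

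Central scenario (31% at or below 0.15, slope 0.8):

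| Model | log OR | SE | mean z | power | relative sample size |
|---|---|---|---|---|---|
| unadjusted | 0.141 | 0.0643 | 2.19 | 59% | 0.63 |
| motor + aphasia | 0.146 | 0.0644 | 2.27 | 62% | 0.67 |
| + two-level split | 0.163 | 0.0647 | 2.52 | 71% | 0.83 |
| + continuous logit | 0.180 | 0.0653 | 2.76 | 79% | 1.00 |

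For the split: (2.52/2.76)² = 0.83, and Φ(2.52 − 1.96) = Φ(0.56) = 0.71. In patients, 0.83 × 3000 = 2490, so about 510 of 3000 are forgone.

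All nine scenarios:

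| at or below 0.15 | slope | z motor + aphasia | z split | z continuous | split, relative size | motor + aphasia, relative size | power, split to continuous |
|---|---|---|---|---|---|---|---|
| 31% | 0.5 | 2.61 | 2.74 | 2.83 | 0.94 | 0.85 | 78.2 to 80.7% |
| 31% | 0.8 | 2.27 | 2.52 | 2.76 | 0.83 | 0.67 | 71.4 to 78.9% |
| 31% | 1.0 | 2.08 | 2.40 | 2.71 | 0.79 | 0.59 | 67.0 to 77.3% |
| 25% | 0.5 | 2.65 | 2.81 | 2.93 | 0.91 | 0.81 | 80.1 to 83.5% |
| 25% | 0.8 | 2.24 | 2.47 | 2.71 | 0.83 | 0.69 | 69.4 to 77.3% |
| 25% | 1.0 | 1.99 | 2.28 | 2.74 | 0.69 | 0.53 | 62.4 to 78.1% |
| 49% | 0.5 | 2.64 | 2.76 | 2.83 | 0.95 | 0.87 | 78.8 to 80.8% |
| 49% | 0.8 | 2.30 | 2.54 | 2.74 | 0.86 | 0.71 | 72.0 to 78.2% |
| 49% | 1.0 | 2.21 | 2.57 | 2.82 | 0.83 | 0.62 | 72.8 to 80.5% |

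The split keeps 69 to 95% and costs 2 to 16 power points. With 200 data sets a mean z has a Monte Carlo error of about 1/√200 = 0.07. The models were fitted to the same data sets, so the ratios are steadier than the levels.

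**Where the gain comes from.** The standard error is 0.0646 to 0.0650 with the split and 0.0647 to 0.0664 with the continuous term, so it does not fall. The log odds ratio rises, from 0.163 to 0.180 in the central case.

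**Cross-check.** A second simulation (odds ratio 1.22, logit N(−1.2, 1.5), slopes 0.4, 0.7 and 1.0, 400 runs) gave mean z of 3.01, 2.84 and 2.68 with the split and 3.09, 3.06 and 3.00 with the continuous term. The squared ratios are 1.05, 1.16 and 1.25, so the split keeps about 95, 86 and 80%.

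**Subgroup covariates.** Motor deficit plus aphasia stands in for the 7.6 set (depression not simulated, whole trial rather than single subgroups). It keeps 53 to 87% of the continuous model's effective sample size, about 8 to 25% below the split. In the central case, with no heterogeneity, the odds ratio is exp(0.146) = 1.16 with this set and exp(0.163) = 1.18 with the split.

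**The case against.** The strongest reply is that nothing in 7.1 is wrong. Adjusting for the minimisation factors is sound and follows the protocol text in section 3, so a continuous term is an improvement and not a correction. That stands. It is also true that the SAP never states the coding in the model. The sponsor may intend a continuous term, but then the SAP needs to say so.

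The size rests on assumptions. That stands too: a weak predictor costs about 5%.

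On the subgroups, levels within a subgrouping are compared under one common covariate set, and the randomised comparison is not biased. That stands. The shift against the overall log odds ratio was 0.008 to 0.024 in the nine scenarios, small beside a standard error near 0.065. The inconsistency is real but modest. The adjusting clause in 7.6 could also be read as belonging to the consent subgrouping alone. The other three would then have no stated covariates, and the remedy is the same.

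Three stronger readings are tempting and not supported:

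- A reader might infer that all the subgroup models drop predicted outcome. The SIS motor and communication models keep the minimisation factors, and one mRS subgrouping is the split itself.
- A reader might infer that the split widens the confidence interval for the primary odds ratio. The standard errors above show otherwise; the loss is in power.
- A reader might infer that the relative risks in 7.2, "relative risks with 95% CI, calculated from the odds ratio", are overstated because a conditional odds ratio is converted. The SAP does not say whether the adjusted or the unadjusted odds ratio is converted, or at what control risk. The formula sits in a cited handbook that is not at hand. No error can be shown.

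**Conclusion.** The point holds as a matter of efficiency and consistency, not of validity or bias. The only form in which predicted outcome is defined for adjustment in 7.1 to 7.5 is a two-level split, although the probability behind it can be calculated for every patient. At N = 3000 the split keeps roughly 70 to 95% of the effective sample size of continuous adjustment, 83% in the central scenario (power 71% against 79%). These figures depend on the assumed effect, mRS distribution and predictor strength, none of which the SAP gives. The direction was the same in every scenario of both simulations.

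The omission of predicted outcome and delay from the mRS subgroup models can be read directly from 7.6 and needs no simulation. Its effect on power is an estimate under the same assumptions. The change is worth making before unblinding, but the trial's conclusions do not depend on it for their validity.

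**What to change.** State in 7.1 to 7.5 that the adjusted models include the logit of the SSV predicted probability as a continuous covariate, taken from the unrounded probability, together with delay, motor deficit and aphasia as defined in 4.1. Keep the unadjusted analysis.

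In 7.6, use the same set in all four mRS subgroup models. Baseline depression may be added to it but should not replace anything. Where the predicted-outcome split is the subgrouping, keep the split for grouping and the continuous term as a covariate. Apply the same continuous coding in the SIS motor and communication models, so that one definition runs through the plan.

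The cost is SAP wording: no new data and no loss of patients. The one downside is that the adjusted odds ratio becomes conditional on a finer covariate and differs slightly from that of the split-adjusted model. In the nine scenarios the log odds ratio moved by 0.005 to 0.034. The SAP should say this, so that the adjusted and unadjusted odds ratios are not expected to coincide.
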